### Sample Size

2.2

The sample size was calculated for the prespecified primary estimand, the adjusted mean between‐group difference in knee ΔPPT averaged across A1, A4, A7, and A10. The target difference of 0.30 kgf/cm^2^ and the standard deviation of 0.70 kgf/cm^2^ were taken from the within‐session knee PPT change in the feasibility trial of Anderheide et al. (2025). Under compound symmetry with four measurements and a within‐participant correlation of 0.60, the standard deviation of the participant‐level mean is 0.586 kgf/cm^2^ [0.70 × √((1 + 3 × 0.60)/4)]. Assuming a correlation of 0.60 between baseline PPT and that mean, covariate adjustment gives a residual standard deviation of 0.469 kgf/cm^2^ [0.586 × √(1 − 0.60^2^)].

With a two‐sided *α* of 0.05% and 80% power, *n* = 2(z_1_−α/_2_ + z_1_−β)^2^σ^2^/δ^2^ gives 38.3, that is 39 evaluable participants per group (R 4.4.1). Allowing for approximately 15% attrition, 45 participants per group will be recruited, a total of 90, retaining at least 38 evaluable participants per group and power close to 80%. The estimate depends on the assumed baseline correlation: 55 and 60 participants per group would be needed for correlations of 0.30 and 0.

Compound symmetry is a planning assumption, since the analysis will select the covariance structure empirically. Because no established minimal clinically important difference exists for EIH assessed by PPT in KOA, 0.30 kgf/cm^2^ is an a priori planning target rather than a clinical threshold.

### Allocation, Randomization, and Blinding

2.3

After eligibility confirmation, informed consent, and baseline assessment, 90 participants will be randomized 1:1 to the CAEG or RNEG. An independent researcher not involved in recruitment, assessment, or intervention delivery will generate the allocation sequence before recruitment using permuted blocks of variable sizes (4, 6, and 8). Allocation codes will be placed in sequentially numbered, opaque, identical, and tamper‐proof sealed envelopes. Recruitment physiotherapists will not have access to the sequence, and each envelope will be opened only after the baseline assessment.

Participants and treating physiotherapists cannot be blinded because of the nature of the interventions. Outcome assessors and the statistician will remain blinded until the database is locked. Participants will be instructed not to disclose group allocation or treatment procedures to the assessor or other participants.

If a session is missed, the responsible researcher will contact the participant within 72 hours, making up to three attempts by telephone, email, or text message. Make‐up sessions will be scheduled within the same week whenever possible.

### Interventions

2.4

The 10‐week treatment duration was selected to provide 30 supervised sessions, a dose that is feasible in clinical practice and consistent with exercise‐based KOA trials (Fitzgerald et al. 2015; Kabiri et al. 2018; Øiestad et al. 2023). Both protocols will be delivered individually by trained physiotherapists using written manuals. Treatment fidelity will be supported by pretrial competency assessment against a standardized checklist, session‐specific checklists, and monthly direct observation of one randomly selected session per therapist by a senior researcher. Adherence to required components, progression decisions, adverse events, and adaptations will be recorded; deviations will prompt feedback and retraining.

#### Cycling‐Based Aerobic Exercise Group

2.4.1

CAEG sessions will be conducted three times per week for 10 weeks on a horizontal stationary electromagnetic bicycle (Kikos, KR5.6). Seat position will ensure comfort, alignment, and a safe knee range of motion of approximately 25°–35° of flexion at the distal pedal position. Cadence will be maintained at 60–80 rpm during training and at 50–60 rpm during warm‐up and cool‐down. Workload will follow the target effort zone in Supporting Information S1: Table S2 (Thompson et al. 2013; Øiestad et al. 2023; Anderheide et al. 2025; Whitfield and Tomlinson 2025). Participants will maintain usual physical activity and avoid new therapies or exercise programs during the intervention.

Each session will include a 5‐minute warm‐up, a progressive training phase, and a 5‐minute cool‐down. Intensity will be prescribed and monitored using the Borg 6–20 Rating of Perceived Exertion (RPE), with RPE recorded at the 3rd minute, every 5 minutes thereafter, at session end, and after any workload adjustment. Heart rate, blood pressure, peripheral oxygen saturation, and NPRS pain intensity will also be recorded before, during, and after exercise.

Training will be adjusted or interrupted if intolerance symptoms, abnormal cardiovascular responses, SpO_2_ < 88–90%, or NPRS ≥ 7 occur during exercise. Progression will occur when, for two consecutive sessions, pain remains ≤ 5 during and immediately after exercise, returns to the pre‐session level by the following day, and RPE remains within the target zone, consistent with the NEMEX pain‐monitoring approach (Ageberg et al. 2010). Recorded variables will include duration, workload, cadence, distance or energy, heart rate, RPE, NPRS, adverse events, and protocol adaptations.

#### Resistance and Neuromuscular Exercise Group

2.4.2

The RNEG includes warm‐ups, resistance exercises, and neuromuscular balance training (Weng et al. 2009; Ageberg et al. 2010; Bennell et al. 2014; Li et al. 2016; Cheung et al. 2017; Torstensen et al. 2018; Anderson et al. 2019; Benner et al. 2019; Hislop et al. 2020). The program will be delivered three times per week for 10 weeks, with at least 24 hours between sessions, and will be divided into weeks 1–5 and weeks 6–10, as detailed in Supporting Information S1: Tables S3 and S4. Sessions will last approximately 60 minutes. Exercises will be performed in up to three sets of 8–12 repetitions in weeks 1–5 and 8–15 repetitions in weeks 6–10, with 90‐s rest intervals (Kabiri et al. 2018).

Loads will be standardized using the one‐repetition maximum test, with pain ≤ 5 on the NPRS for weighted exercises. Training loads will be set at 40–60% of 1‐RM (Toigo and Boutellier 2006; Rabelo et al. 2014). For elastic bands, resistance will be selected to allow 12 repetitions with NPRS ≤ 5; for bodyweight exercises, holding time will be used as the progression parameter.

Vital signs and pain intensity will be monitored before, during, and after each session. The physiotherapist will provide instructions, ensure safety, and adjust exercise execution. Exercises involving weights, elastic resistance, or contraction duration will be reassessed weekly. Progression will consist of increasing machine load by 5–10%, selecting a higher‐resistance band, or increasing holding time when pain remains ≤ 5 during and immediately after exercise and returns to the pre‐session level by the following day (Ageberg et al. 2010).

### Primary Outcome

2.5

The primary outcome is EIH in the medial knee compartment of the most symptomatic knee, measured as intra‐session change in PPT (ΔPPT) at A1, A4, A7, and A10. The primary estimand is the adjusted mean between‐group difference in ΔPPT averaged across the four sessions. The group‐by‐session interaction and session‐specific differences will be exploratory. PPT will be measured immediately before and after each selected session, and ΔPPT will be the mean post‐exercise value minus the mean pre‐exercise value in kgf/cm^2^. Positive values indicate EIH, zero indicates no EIH, and negative values indicate a hyperalgesic response. If both knees are equally symptomatic, the target knee will be predefined and maintained throughout the trial.

PPT will be measured using a digital algometer (Force Ten FDX‐25, Wagner Instruments, Greenwich, USA) using a 1 cm^2^ probe. Pressure will be applied at 0.5 kgf/s until the sensation first becomes painful and the participant indicates “stop” (Rolke et al. 2006; Anderheide et al. 2025). Three readings will be obtained at the target knee using the same evaluator, in the same order, with 30‐s intervals. The arithmetic mean will be used for analysis, and skin marking will be used to improve site reproducibility.

The knee PPT site will be the medial compartment at the joint line, 2–3 cm medial to the inferomedial angle of the patella, with the participant supine. Intra‐session EIH will be calculated only at A1, A4, A7, and A10. T0 and T1 PPT assessments will characterize baseline and post‐intervention pressure pain sensitivity, not acute EIH.

### Secondary Outcomes

2.6

Secondary EIH outcomes are intra‐session ΔPPT at the rectus femoris and upper trapezius at A1, A4, A7, and A10. Rectus femoris PPT will be assessed bilaterally with the participant supine, 15 cm proximal to the base of the patella. Upper trapezius PPT will be assessed bilaterally with the participant seated and 10 cm medial to the acromion at the level of C7. For bilateral sites, the right and left values will be averaged for analysis. Chronic adaptation in PPT will be evaluated at T0 and T1 at the knee, rectus femoris, and trapezius.

CPM will be assessed at T0 and T1 using conventional PPT as the test stimulus and ischemic compression as the conditioning stimulus, consistent with CPM testing recommendations (Yarnitsky et al. 2015). Baseline PPT will be measured on the anterior surface of the right forearm, 7.5 cm from the distal wrist crease, using the same algometer and an application rate of 0.5 kgf/s. PPT algometry demonstrates acceptable to excellent reliability in people with KOA (Stausholm et al. 2023). For the conditioning stimulus, an aneroid sphygmomanometer was positioned on the left arm, 3 cm proximal to the cubital fossa, and inflated to 250 mmHg. If pain is < 5 on the NPRS, participants will perform elbow flexion and extension until pain reaches ≥ 5. PPT will then be reassessed on the right forearm while the conditioning stimulus is maintained. After cuff release, PPT will be reassessed at 30 seconds and 5 minutes. CPM will be calculated as the change in PPT during conditioning relative to baseline PPT, with higher values indicating more efficient modulation.

Pain intensity will be assessed at T0 and T1 using the Brazilian Portuguese Numerical Pain Rating Scale (NPRS), ranging from 0 (“no pain”) to 10 (“worst imaginable pain”), for average pain at rest and after movement over the previous 7 days. A 2‐point change will serve as the reference threshold for clinical interpretation (Farrar et al. 2001; Costa et al. 2008).

Pain self‐efficacy will be assessed at T0 and T1 using the Brazilian Portuguese Pain Self‐Efficacy Questionnaire (PSEQ), a 10‐item scale scored from 0 to 60, with higher scores indicating greater self‐efficacy. An 11‐point change will serve as the reference threshold for clinical interpretation (Sardá et al. 2007; Dubé et al. 2021).

Knee health status will be assessed at T0 and T1 using the Brazilian Portuguese Knee Injury and Osteoarthritis Outcome Score (KOOS), which includes the Pain, Symptoms, Activities of Daily Living, Sport/Recreation, and Knee‐Related Quality of Life subscales. Scores will be transformed into a 0–100 scale, with higher scores indicating better status. A 10‐point change per subscale will serve as the reference threshold (Roos and Lohmander 2003; Almeida et al. 2022; Pathak et al. 2022).

Patient‐specific function will be assessed at T0 and T1 using the Patient‐Specific Functional Scale (PSFS), in which participants identify three KOA‐related activities and rate each on a scale from 0 to 10. The score is the mean of the three activities, and the same activities identified at baseline will be re‐rated at T1. PSFS has strong measurement properties across musculoskeletal conditions, and changes of ≥ 2 points are generally considered clinically meaningful (Moore et al. 2020; Dubé et al. 2021; Pathak et al. 2022).

Lower‐limb functional performance will be assessed at T0 and T1 using the 30‐s sit‐to‐stand test (30STST), recommended by OARSI for KOA. Using a 43 cm armless chair against a wall, participants will keep their arms crossed and complete as many full repetitions as possible in 30 seconds after 1–2 practice repetitions. The score will be the number of full repetitions completed (Dobson et al. 2013; Gill et al. 2022).

Quadriceps strength will be assessed at T0 and T1 using maximal voluntary isometric contraction (MVIC) measured with a handheld dynamometer (Lafayette Manual Muscle System, Model 01163). Participants will sit with their hips at 90° and knees at 60°. The dynamometer will be positioned at the malleolar level and secured with a non‐elastic strap during knee extension. Force will be normalized to body weight (Martin et al. 2006; de Paula Gomes et al. 2018).

Global perceived effect will be assessed at T1 using an 11‐point scale ranging from −5 (“much worse”) to +5 (“completely recovered”), with a 2‐point change serving as the reference threshold for clinical interpretation (Kamper et al. 2009). Adherence will be calculated as attendance (%) = (attended sessions/planned sessions) × 100.

Exercise enjoyment will be assessed at T1 using the Brazilian Portuguese Physical Activity Enjoyment Scale (PACES), an 18‐item, 7‐point bipolar‐response scale measuring perceived enjoyment during exercise. After recoding the required items, higher scores indicate greater enjoyment. The Brazilian Portuguese version demonstrated almost perfect reproducibility, with a minimal detectable change of 23.9 points (Alves et al. 2019).

## Statistical Analysis

3

Statistical analyses will follow the intention‐to‐treat principle. The primary outcome will be analyzed using a linear mixed model with fixed effects for group, assessment session (A1, A4, A7, and A10), and group‐by‐session interaction; baseline PPT at the corresponding site will be included as a covariate, with a random intercept for participants.

The primary treatment effect will be the adjusted mean between‐group difference in ΔPPT averaged across the four sessions, estimated using marginal means with 95% confidence intervals and *α* = 0.05. The group‐by‐session interaction and session‐specific contrasts will be exploratory. The covariance structure will be selected using the Akaike Information Criterion from prespecified compound‐symmetry, autoregressive, and unstructured structures.

Continuous secondary outcomes measured at T0 and T1, including KOOS, 30STST, NPRS, CPM, PSEQ, PSFS, and MVIC, will be analyzed using linear mixed models with fixed effects for group, time, and group‐by‐time interaction and a random participant intercept. T1‐only outcomes, including PACES and GPE, will be analyzed using regression models with group as the predictor and an appropriate link function if distributional assumptions are not met.

The primary outcome will be the sole confirmatory outcome because the trial is powered only for it. All secondary outcomes are prespecified but will be interpreted as exploratory and supportive, with emphasis on effect sizes and 95% confidence intervals rather than on confirmatory hypothesis testing.

Clinically important thresholds, when available, will be used only as reference values to support interpretation and not as confirmatory decision rules.

Mixed models will use all available data under the missing‐at‐random assumption. For outcomes not accommodated by mixed models, multiple imputation by chained equations will be used when more than 5% of observations are missing, incorporating group, available baseline and outcome values, adherence, and predictors of missingness. Complete‐case analyses will be sensitivity analyses only. Adherence will be summarized as attendance percentage; a per‐protocol sensitivity analysis will define adequate adherence as ≥ 80%. Protocol deviations, adverse events, and adaptations will be summarized descriptively. Analyses will be conducted in *R*.

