### Study Design and Recruitment

2.1

This randomized, two‐arm, controlled, single‐blind clinical trial will be conducted at the University Clinics of the Nove de Julho University in São Paulo, Brazil. The protocol adheres to the updated CONSORT 2025 and SPIRIT 2025 recommendations and uses the Template for Intervention Description and Replication (TIDieR) checklist to support transparent reporting of the intervention (Hoffmann et al. 2014; Chan et al. 2025; Hopewell et al. 2025) (Supporting Information S1: Table S1).

Recruitment will occur through posters, leaflets, educational talks, and referrals from clinic staff. The target is approximately five eligible participants per month, though this may vary with screening availability and changes in baseline EIH. Screening will include initial contact, informed consent, clinical eligibility assessment, baseline assessment, and randomization only after baseline procedures.

This study was approved by the Research Ethics Committee of Nove de Julho University (No. 93560425.7.0000.5511) and prospectively registered on ClinicalTrials.gov (identifier NTC07302204). Planned recruitment and follow‐up will run from April 2026 to December 2029, aligned with the doctoral timeline and trial logistics. Recruitment may end earlier if the target sample is reached. The same research setting, recruitment sources, and core research team will be maintained throughout the study, whenever possible, to minimize protocol drift and ensure consistency in eligibility assessment, outcome measurement, and intervention delivery.

Recruitment and eligibility assessment will be conducted by two trained physiotherapists using a standardized checklist (Fitzgerald et al. 2015). Before recruitment, the blinded outcome assessor will complete standardized PPT training and a test‐retest reliability assessment in 15 people with KOA. Reliability of the mean of three readings will be estimated using a two‐way mixed‐effects, absolute‐agreement ICC, the standard error of measurement (SEM), and the 95% minimal detectable change (MDC95). An ICC ≥ 0.80 will be required; otherwise, retraining and reassessment will be performed (Stausholm et al. 2023).

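### The T0/T1 secondary outcomes are modelled with free baseline means, which leaves the estimates unbiased but less precise than a common T0 mean would make them

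*Protocol article*

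**What the plan says.** The Statistical Analysis section groups together "Continuous secondary outcomes measured at T0 and T1, including KOOS, 30STST, NPRS, CPM, PSEQ, PSFS, and MVIC" and says that they "will be analyzed using linear mixed models with fixed effects for group, time, and group‐by‐time interaction and a random participant intercept". It names no baseline covariate for them and does not constrain the two arms to a common T0 mean. It also does not say whether the reported effect will be the group-by-time coefficient or the T1 difference in marginal means.

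For the primary outcome the same section does adjust: "baseline PPT at the corresponding site will be included as a covariate, with a random intercept for participants".

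The Study Design and Recruitment section places "randomization only after baseline procedures", and the allocation section has each envelope opened only after the baseline assessment. The secondary outcomes "will be interpreted as exploratory and supportive, with emphasis on effect sizes and 95% confidence intervals". PPT at T0 and T1 is also a secondary outcome (Secondary Outcomes section), although the list in the analysis section does not name it.

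**The concern.** T0 is measured before allocation, so any difference between the arms at T0 is chance. A model with a free group effect spends information on estimating a difference that the design sets to zero in expectation. It then subtracts the whole of the observed T0 imbalance, where regression to the mean calls for subtracting only part of it.

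The stake is the width of the intervals and their stability in a trial of 90 people. That matters because these outcomes are to be read through effect sizes and 95% CIs, alongside reference thresholds for NPRS, PSEQ, KOOS and PSFS. No confirmatory claim depends on them.

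**Working it through.** **The plan's own use of baseline adjustment.** The article gives no precision figure for the T0/T1 outcomes. The only related figure is for the primary outcome, in the Sample Size section. The SD of the four-session mean is 0.70 × √((1 + 3 × 0.60)/4) = 0.586. With a baseline correlation of 0.60 the residual SD is 0.586 × √(1 − 0.36) = 0.469. At two-sided α = 0.05 this gives n = 38.3, so 39 per group; with correlations of 0.30 and 0 it gives 55 and 60. All match the article. The plan therefore already relies on baseline adjustment where it sizes the trial.

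**Inputs for the secondary outcomes.**
- Two time points, 1:1 allocation, 45 per arm, about 15% attrition (Sample Size and allocation sections).
- T0–T1 correlation ρ: not given, so assumed from 0.4 to 0.9.
- T0 and T1 variances: not given, first assumed equal (σ²).

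**Step 1: what the planned model estimates.** With complete pairs, the group-by-time coefficient is the difference in mean change. Fitting the stated model to simulated complete data confirmed this: the largest discrepancy was 2 × 10⁻¹⁵.

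**Step 2: variance.** In units of 2σ²/n:
- planned contrast: 2(1 − ρ)
- baseline-adjusted contrast (ANCOVA or common T0 mean): 1 − ρ²
- ratio, adjusted to planned: (1 − ρ²)/[2(1 − ρ)] = (1 + ρ)/2

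| ρ (assumed) | Variance ratio | CI narrower by 1 − √ratio |
|---|---|---|
| 0.4 | 0.70 | 16% |
| 0.5 | 0.75 | 13% |
| 0.6 | 0.80 | 11% |
| 0.7 | 0.85 | 8% |
| 0.8 | 0.90 | 5% |
| 0.9 | 0.95 | 3% |

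**Step 3: missing T1 values.** Participants with T0 only contribute a little to the planned model, so the identity in Step 1 becomes approximate. With 15% of T1 missing completely at random, the variance of the planned contrast relative to the constrained one is 1 + 0.85 × (1 − ρ)/(1 + ρ). At ρ = 0.6 this is 1 + 0.85 × 0.4/1.6 = 1.21, against 1.25 with complete pairs. A simulation of 20,000 trials with known covariance also gave 1.21. Most of the loss remains.

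**Step 4: unequal variances.** Let k be the T1 SD divided by the T0 SD. In units of the T0 variance, the change variance is 1 + k² − 2ρk and the adjusted variance is k²(1 − ρ²). At ρ = 0.5:
- k = 1.25: 1.172/1.3125 = 0.89
- k = 1.5: 1.6875/1.75 = 0.96

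The gain vanishes where ρk = 1, because the best baseline coefficient, ρk, is then the 1 that a change score imposes.

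**Step 5: chance imbalance.** With equal variances, an observed T0 difference of d SDs moves the change contrast by −(1 − ρ)d relative to the adjusted one. With 45 per arm the standard error of d is √(2/45) = 0.21 SD. At ρ = 0.5, an imbalance of one standard error moves the estimate by 0.5 × 0.21 ≈ 0.11 SD.

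**Step 6: if the T1 marginal difference is reported instead.** With complete data the planned model returns the raw T1 difference, with variance 1 in the units of Step 2. The adjusted variance is again 1 − ρ², so the adjusted estimate is more precise under either reading (ratio 0.75 at ρ = 0.5, 0.51 at ρ = 0.7).

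**The case against.** The strongest reply is that this is a matter of efficiency and not an error. Under randomization the planned contrast is unbiased, the outcomes are declared exploratory, the thresholds are reference values only, and no sample size rests on these intervals. All of that stands, and it limits the weight of the point.

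Four stronger readings are tempting, and the documents do not support them.

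- A reader might infer that the planned analysis is biased. It is not, over randomizations; the cost is precision and sensitivity to the imbalance that happens to occur.
- A reader might infer that the model simply is a change-score analysis. That is exact only with complete pairs. The article plans for about 15% attrition and uses all available data in its mixed models.
- A reader might infer one fixed gain for all seven instruments. No T0–T1 correlation or variance is given for any of them. The NPRS entry criterion of at least 3 points may compress the T0 spread relative to T1, which is the direction in which a moderate excess of T1 variance reduces the gain.
- A reader might see a contradiction with the primary model, where "baseline PPT at the corresponding site will be included as a covariate". The primary response is change within sessions A1 to A10, and T0 is not a response in that model, so baseline can enter only as a covariate. In the T0/T1 models T0 is itself a response. The data structures differ. The comparison shows only that the plan already values baseline adjustment.

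It can also be said that ANCOVA is not free of cost, because it drops participants without T1 unless their values are imputed. That is correct, and it is why the constrained model is the better remedy.

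**Conclusion.** The point holds as a modest loss of precision in a model that the article states outright. Assuming complete pairs and equal T0 and T1 variances, the constrained model would have 0.70 to 0.95 of the planned variance for ρ from 0.4 to 0.9, with intervals about 16% to 3% narrower. Planned attrition reduces this only slightly. A moderately larger T1 variance reduces it more, to a ratio of 0.89 at ρ = 0.5 with an SD ratio of 1.25. The size for each instrument cannot be fixed from the document. The change is worth making because it uses data already collected and these outcomes are interpreted through their intervals.

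**What to change.** For all continuous T0/T1 outcomes, naming T0/T1 PPT among them, replace the stated model with a constrained longitudinal model: a common T0 mean, effects for time and group-by-time, no group main effect, and an unstructured 2×2 covariance in place of the random intercept, so that T0 and T1 variances may differ. State that the reported effect is the adjusted T1 between-group difference with its 95% CI. This keeps participants who have T0 only and fits the missing-at-random approach already chosen. ANCOVA of T1 on group and T0 is acceptable if the plan also says how missing T1 values are handled.

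The cost is a sentence or two of analysis wording, settled before unblinding. No additional data or participants are needed.
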